### Secondary behavioral outcomes

To assess change in alcohol-related approach bias and cognitive performance, we will use the Approach Avoidance Assessment approach bias score (reaction time in seconds; alcohol-push minus alcohol-pull). To determine whether AAT engages the target as hypothesized (i.e., improving approach bias), we will analyze the effect of AAT versus the Sham group in a mixed effects model repeated measure approach as in Aim 1.

### Secondary MRI outcomes

#### Single subject analysis

Imaging data will be collected on Siemens 3T Prisma scanner. The Alcohol Approach Avoidance Assessment task will be scanned with echo-planar imaging (EPI) sequences and a high-resolution anatomical image will also be collected. Data preprocessing will occur with our standard pipelines with AFNI and ANTsR software [51, 52]. To assess approach bias, individual task regressors will be generated for each participant to account for individual differences in response and movement speed. Task activation maps for push conditions will then be subtracted from the pull conditions to create the primary contrast of interest [alcohol pull-push > neutral pull-push].

#### Neuroimaging group level analysis

Linear mixed effects models will be used to evaluate whether BOLD activation changes differentially over time and group (AAT training versus Sham) for the primary contrast of interest. The primary fMRI outcome is the difference in BOLD response to the alcohol pull-push > neutral pull-push contrast, which is a continuous outcome variable reflecting differential activation to the task conditions at each voxel of the brain. We will use a threshold adjustment based on Monte-Carlo simulations (AFNI’s 3dClustSim) to ensure Type I error is controlled when interpreting significant brain clusters that are active. The simulations will be generated in a single mask of three a priori anatomical regions of interest (ROIs) previously identified as impacted by AAT in the context of an RCT to treat AUD, including the bilateral amygdala, mPFC, and striatum. The linear mixed effects model conducted in AFNI 3dLME will include condition (AAT vs. Sham) as a between-subject factor and time (baseline, post-training) as the within-subjects factor, with participant included as a random factor. The hypothesis that AAT recipients, relative to Sham recipients, will demonstrate reduced approach bias would be supported by an interaction of condition by time on BOLD activation in the primary contrast of interest.

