### Sample size

Sample size determinations for the functional outcomes were made with a series of power calculations conducted using RMASS power calculation software for longitudinal mixed models. Parameters entered into the calculation included an effect size of d = 0.6 [32], 4 time points, attrition ranges between 20 and 25% based on rates in a prior VA-based clinical trial with a similar sample [47], and α = 0.05. Under the most conservative retention rate, we will need to enroll 136 participants to achieve 80% power. Sample size determinations for imaging outcomes were made using R:WebPower software for analysis of variance for a treatment group x time interaction term. Parameters entered into the calculation included an effect size of d = 0.80, 2 time points, and attrition as above with α = 0.05. We will need a sample of n = 51 to achieve 80% power to detect a treatment group x time effect on the regions encompassed within our a priori mask.

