## Outcomes and statistical methods

### Primary and secondary clinical outcomes

To evaluate whether AAT significantly improves clinical outcomes relative to Sham, a mixed effects model repeated measures (MMRM) model will be used. The dependent variable in the MMRM model is change from baseline in AUD-related disability (DrInC) at each post-baseline visit (post visit, 3 and 6 mo. follow-up). Predictors in the model will include treatment condition (AAT, Sham), visit (immediately post-training, 3 and 6 mo.), condition by visit interaction term, and baseline DrInC. The primary end point is the post-training visit. The same analytic approach will be applied to the secondary outcome (PDHD). We will model the distribution of percent days heavy drinking to ensure appropriate analysis. All subjects randomized will be included in the intent-to-treat analysis. Depending on the type of missing data, the appropriate statistical approach (e.g., multiple imputation) will be determined. Sensitivity analyses will be used to explore the impact of missing data.

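### The fMRI condition-by-time test is valid but less efficient than the baseline-adjusted model planned for the other outcomes; adjusting it would gain precision without extra data

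*Protocol article*

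**What the plan says.** The Protocol article fixes the imaging model in Neuroimaging group level analysis. It is a linear mixed model in AFNI 3dLME with "condition (AAT vs. Sham) as a between-subject factor and time (baseline, post-training) as the within-subjects factor, with participant included as a random factor". The hypothesis "would be supported by an interaction of condition by time on BOLD activation in the primary contrast of interest". No baseline covariate is named, and the arms are not constrained to share a baseline mean.

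The sample size section is consistent with this. It powers imaging by "analysis of variance for a treatment group x time interaction term", with d = 0.80, two time points and alpha 0.05, and arrives at n = 51 for 80% power.

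The clinical outcomes are handled differently. In Primary and secondary clinical outcomes, "The dependent variable in the MMRM model is change from baseline in AUD-related disability (DrInC) at each post-baseline visit", and the predictors include the "condition by visit interaction term, and baseline DrInC". The same approach is stated for percentage days heavy drinking. Secondary behavioral outcomes analyses the approach bias score "in a mixed effects model repeated measure approach as in Aim 1", so baseline adjustment carries over there by reference only.

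**The concern.** Randomisation makes the expected baseline contrast equal in the two arms. A model that estimates a separate baseline mean for each arm spends information on a difference known to be zero in expectation, and any chance difference at baseline passes partly into the estimated effect. The plan avoids this for the clinical outcomes but not for imaging, which has the smaller sample (51, against 136 for the trial), and it gives no reason for the difference.

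At stake is the precision of one of the two measures serving the secondary aim, whether training reduces approach bias. The baseline scan needed for the more precise estimate is already being collected.

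**Working it through.** **Inputs from the Protocol article.** d = 0.80, two time points, alpha 0.05 (taken as two-sided), n = 51, 80% power and attrition of 20 to 25% (Sample size); 1:1 allocation between AAT and Sham (Allocation).

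**Assumed inputs.** r, the correlation between baseline and post-training contrasts, is not given; 0.3, 0.5 and 0.7 are shown. The variance is taken as equal at both scans.

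**Step 1: the plan's own figure.** For a 2 x 2 group-by-time interaction with f = d/2 = 0.40 and 1 and N - 2 degrees of freedom, N = 51 gives power 79.96% (N = 52 gives 80.7%). This is the same as a two-sided two-sample t test on change scores with d = 0.80 in change-score SD units. So n = 51 is reproduced, as a number analysed.

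**Step 2: what the planned interaction estimates.** On simulated complete two-visit data, a random-intercept REML fit and a change-score t test gave the same estimate and t value: 0.4898 and t = 1.785 at r = 0.2; 0.7543 and t = 2.579 at r = 0.5.

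**Step 3: variance with complete data.** In units of the single-scan variance, and up to a common factor for sample size:

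- Planned interaction: 2(1 - r)
- Baseline-adjusted: 1 - r²
- Ratio: (1 - r²) / [2(1 - r)] = (1 + r)/2

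This gives 0.65, 0.75 and 0.85 at r = 0.3, 0.5 and 0.7, so the reductions are 35%, 25% and 15%.

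**Step 4: variance with dropout.** The mixed model also uses participants with a baseline scan only. With a fraction p lost completely at random, and relative to a change-score comparison among completers:

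- Planned interaction: [(1 + r) + (1 - r)(1 - p)]/2. At p = 0.25 this is 0.9125, 0.9375 and 0.9625.
- Baseline-adjusted: (1 + r)/2, as before.
- Ratio: 0.65/0.9125 = 0.712; 0.75/0.9375 = 0.800; 0.85/0.9625 = 0.883.

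The reductions are then about 29%, 20% and 12%.

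**Step 5: power as a single-outcome illustration.** Take d = 0.80 on the change-score SD. Dividing 0.80 by the square root of each factor gives an effective d of 0.992, 0.924 and 0.868 after adjustment, and of 0.837, 0.826 and 0.815 for the planned model with 25% dropout. If 51 are scanned, 51 x 0.75 leaves about 38 completers.

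| r | 51 analysable: planned | 51 analysable: adjusted | 51 scanned, about 38 complete: planned | 51 scanned, about 38 complete: adjusted |
|---|---|---|---|---|
| 0.3 | 80% | 93.5% | 71% | 85% |
| 0.5 | 80% | 89.9% | 70% | 79% |
| 0.7 | 80% | 85.9% | 69% | 74% |

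At r = 0.8 the gain shrinks further: from 80% to 83.9% with 51 analysable, and from about 68% to about 72% with 38 completers.

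If d = 0.80 is instead on the single-scan SD, power with 51 analysable goes from 60.0% to 81.5% (r = 0.2), from 80.0% to 89.9% (r = 0.5) and from 95.1% to 97.5% (r = 0.7).

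**Step 6: chance imbalance.** With 19 per arm, the standard error of the baseline difference is sqrt(2/19) = 0.32 SD. A change score passes on (1 - r) of an imbalance, so at r = 0.5 one standard error moves the estimate by 0.16 SD, a fifth of a 0.80 SD effect.

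**The case against.** The strongest reply is that nothing here is wrong. The interaction test is unbiased under randomisation and keeps its type I error. It is also the test the imaging sample was powered for, and the Background describes a time-by-group interaction in an earlier imaging study of this training, so keeping it helps comparability. That stands. It makes this an improvement in efficiency rather than the correction of an error, but it does not make the extra variance necessary.

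Four stronger readings are tempting, and the documents do not support them:

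- **That the interaction uses only participants with both scans.** A reader might infer this from the change-score equivalence. The equivalence is exact only without dropout. The planned mixed model draws some information from baseline-only participants, so a completers-only comparison (67% power at 38) understates it; 69 to 71% is the fair starting point.
- **That the powers above are those of the planned test.** They are for one outcome at alpha 0.05. The plan tests voxelwise with a cluster threshold from simulation, and that power cannot be derived from the stated inputs.
- **That attrition certainly reduces the imaging sample below 51.** The text does not settle whether 51 is counted before or after attrition, so both cases are shown.
- **That every other outcome names a baseline covariate.** It is explicit for DrInC, carried over by a same-approach statement for percentage days heavy drinking, and inferred from the reference to Aim 1 for behavioural bias.

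**Conclusion.** The concern holds as a matter of efficiency and consistency in a secondary outcome. The planned imaging test is valid, and the primary conclusion of the trial is not affected. It nevertheless gives up precision that a baseline-adjusted model of the same effect would keep: 15 to 35% of the variance with complete data and about 12 to 29% with 25% dropout, for r from 0.7 down to 0.3.

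These sizes rest on the assumed r, on equal variance at the two scans and, for the dropout figures, on loss completely at random. The gain is large at low to moderate r and small at 0.8 or above; the variance ratio stays below 1 for every r below 1. The power figures also depend on the scale of d, which the Protocol article does not state. A reader might take the finding to mean that the imaging result would be biased; it would not.

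**What to change.** In Neuroimaging group level analysis, replace the unconstrained interaction with one of these, and name which:

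- Keep the mixed model but constrain the arms to a common baseline mean: a time term plus a term for AAT at post-training, with no condition main effect. This keeps participants with only a baseline scan in the model.
- Regress the post-training contrast on condition, with each participant's own baseline contrast as covariate (voxelwise, or as the mask mean).

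Make the treatment term of the chosen model the test of the imaging hypothesis. Fix the choice before unblinded analysis, because choosing between models afterwards would invite selective reporting. A covariate for age stratum is not needed for this point.

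The cost is a change of model specification and its set-up in the imaging software. No further scan, participant or procedure is required.

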### Data management and dissemination

All data entry and management will be conducted in accordance with requirements by the VA San Diego Health Care System and the Standards for Privacy of Individually Identifiable Health Information (“Privacy Rule”) of the Health Insurance Portability Act of 1996 (“HIPAA”). To increase confidentiality, all data will be de-identified prior to data entry into secure databases. To ensure data quality, data will be double entered. Analysis and publication of the study results will be conducted by the investigative team without the involvement of external professional writers. All personnel who have had a significant role in development, analysis, or writing will have the right to authorship of the manuscript reporting the primary outcomes. JB and [name] will determine authorship of manuscripts reporting additional secondary analyses based on the individuals’ role to the aspects of the study being reported.

## Discussion

This study protocol described a double-blind randomized controlled trial to assess the clinical utility of AAT as an adjunctive treatment to standard care in Veterans with AUD and comorbid psychiatric disorders. Prior research supports the use of AAT as an adjunctive treatment for substance use disorders [34, 44, 53–55] and emerging research suggests that variations of cognitive training for approach/avoidance biases may be beneficial for symptoms of other psychiatric disorders [29, 56, 57]. However, the impact of AAT treatment on alcohol consumption and functional recovery outcomes in Veterans with AUD and comorbid psychiatric disorders remains unaddressed. The present study protocol aims to address this gap by including comprehensive assessments of functional recovery in addition to investigating if AAT reduces approach bias for alcohol cues as measured at the behavioral and neural level.

One strength of the study design is the comprehensive evaluation of changes in approach bias across behavioral and neural indicators. Previous research suggests AAT may modify neural regions implicated in alcohol addiction and relapse (e.g., mesolimbic regions) [45], resulting in greater reductions in cue-elicited activation in the bilateral amygdala and decreased craving in alcohol dependent individuals [44]. Assessing changes in brain response to AAT may provide evidence to validate the proposed model suggesting that aberrant approach bias, driven by incentive salience dysfunction, is a modifiable factor underlying pathological alcohol use.

It is important to address potential limitations and possible mitigation approaches associated with conducting the proposed study. The main challenges include treatment adherence, participant retention, and study completion since dropout rates for addiction treatments are high, especially in comorbid populations [58, 59]. As attrition rates are anticipated to range between 20 and 25%, participants will be overrecruited to ensure the study is well powered to examine treatment effects. The treatment protocol includes 12 sessions, administered twice a week for 6 weeks, which can be demanding for participants who are also receiving concurrent clinical care. AAT treatment sessions will therefore be made as convenient as possible by allowing in-person or remote appointments, depending on participant preference, in order to reduce participant burden. Procedures will also be put in place to remind participants of their appointments and provide opportunities to easily reschedule missed treatment sessions. To support retention, participants are asked to provide mobile phone numbers, home addresses, and a secondary phone contact to ensure treatment reminders are received in a timely manner. Participants are compensated for study participation after completion of each follow-up appointment. Task-based adherence data will be collected during the computerized treatment sessions to assess if participants are engaging sufficiently in treatment sessions.

In conclusion, the current study will test AAT with standard care in Veterans given evidence that this may be a promising adjunctive treatment for individuals with AUD and comorbid psychiatric disorders. If found effective, AAT could serve as a non-invasive, low cost, mechanistic specific treatment targeting approach bias by using a cognitive training procedure designed to reduce approach bias toward alcohol cues. This new treatment approach has the potential to reduce healthcare costs by improving recovery outcomes for Veterans and consequently reducing treatment readmittance. In addition, offering AAT as an adjunctive treatment to standard care presents a relatively low financial burden with high potential for successful outcomes. Research findings are anticipated to contribute valuable data to the field by demonstrating links between approach bias shifts and clinical outcomes with an interdisciplinary study design. This trial will further our understanding of AAT treatment mechanisms and provide valuable clinical data on AUD-related functional outcomes in Veterans with comorbidities.

## Data Availability

The datasets generated during the current study will not be publicly available but are available from the corresponding author on reasonable request in consideration of VA data management and access plan policies. For further information about the protocol, all items from the World Health Organization Trial Registration Data Set are detailed in the appendix table.
